## Abstract

**Background:**

The value of chemotherapy in soft tissue sarcoma (STS) remains controversial. Several expert teams consider that chemotherapy provides a survival advantage and should be proposed in high-risk (HR) patients. However, the lack of accuracy in identifying HR patients with conventional risk factors (large, deep, FNCLCC grade 3, extremity STS) is an issue that cannot be neglected. For example, while the FNCLCC grading system is a powerful tool, it has several limitations. CINSARC, a 67-gene signature, has proved to be an additional independent factor for predicting metastatic spread and outperforms histological grade. Regardless of FNCLCC grade, CINSARC stratifies patients into two separate prognostic groups: one with an excellent prognosis (low-risk (LR) CINSARC) and the other with a worse outcome (HR-CINSARC) in terms of metastatic relapse. Here we evaluate the role of chemotherapy in grade 1–2 STS patients with HR-CINSARC and assess the prognostic value of CINSARC in patients treated with standard of care.

**Methods:**

CHIC is a parallel, randomized, open-label, multicenter study evaluating the effect on metastasis-free survival of adding perioperative chemotherapy to standard of care in patients with grade ½ STS sarcoma defined as HR by CINSARC. In this target selection design, 600 patients will be screened with CINSARC to randomize 250 HR-CINSARC patients between standard of care and standard of care plus chemotherapy (4 cycles of 3 weeks of intravenous chemotherapy with doxorubicin in combination with dacarbazine or ifosfamide according to histologic subtype). LR-CINSARC patients will be treated by standard of care according to the investigator. The primary endpoint is metastasis-free survival. Secondary endpoints include overall survival, disease-free survival and safety. Furthermore, the prognostic value of CINSARC will be evaluated by comparing LR-CINSARC patients to HR-CINSARC patients randomized in standard of care.

**Discussion:**

CHIC is a prospective randomized phase III trial designed to comprehensively evaluate the benefit of chemotherapy in HR-CINSARC patients and to prospectively validate the prognostic value of CINSARC in grade ½ STS sarcoma patients.

**Trial registration:**

ClinicalTrials.gov identifier: NCT04307277 Date of registration: 13 March 2020

## Background

With an incidence of 4–5 cases / 1,000,000, soft tissue sarcomas (STS) are a group of rare heterogeneous tumors that develop from connective tissue cells. Their therapeutic management is based on multidisciplinary discussion at every step, starting with the need for a pre-therapeutic diagnostic biopsy. The key point in treating patients with localized STS is a large surgical resection to obtain a microscopically negative margin and remove all tumor cells. The quality of surgery remains the main risk factor for metastatic relapse. Neo-adjuvant or adjuvant treatments (radiotherapy and/or chemotherapy) are discussed case by case in a multidisciplinary meeting, depending on the presence of other prognostic factors such as histologic subtype, tumor size and FNCLCC (Fédération Nationale des Centres de Lutte Contre le Cancer) grade.

In recent decades, the role of perioperative (mainly adjuvant) chemotherapy in patients with localized STS has been extensively investigated. Currently, even after multiple randomized studies supplemented by two meta-analyses [1, 2] the survival benefit of chemotherapy in all patients with localized STS remains debated. In current guidelines [3], chemotherapy may be proposed as an option in HR patients but it is not part of standard of care. This uncertainty regarding the real impact of chemotherapy can be explained by the diversity of the randomized studies in terms of drug type, tumor grade, location, and quality of surgery, each of these factors being essential. Based on previous published studies, many expert teams currently consider that chemotherapy provides a survival advantage and should be proposed in HR patients [4]. This HR subgroup includes patients with large, deep, high FNCLCC grade, and extremity STS [5]. One study specifically included these patients yet showed an improvement in survival [6]. However, the debate concerning the value of chemotherapy in localized STS is currently in deadlock, mirroring the difficulty of accurately identifying HR patients by using conventional factors, and more specifically the FNCLCC grade. This grading system, which splits STS into three grades (1, 2 or 3), remains the best predictor of metastatic relapse available in localized sarcoma [5, 7]. Despite its consensual use in determining the optimal therapeutic strategy of patients with STS [8], it has several limitations. It is not applicable in all pathological subtypes, it shows variable reproducibility between pathologists, and it is difficult to use with tumor microbiopsies, i.e. the gold standard for diagnosis. Above all, however, FNCLCC grade has a poorly informative prognostic value for grade 2, which represents about 40% of all STS. Therefore, the CINSARC signature, which is especially informative in patients with intermediate-grade tumors, could be a way out of this “never-ending story”.

### CINSARC signature

In 2010, Chibon et al. identified a 67-gene expression signature, CINSARC (Complexity Index in SARComas), and validated it as an independent prognostic factor in several STS histotypes [9]. They also demonstrated that it outperformed histologic grade and was able to split STS into two separate prognostic groups, regardless of FNCLCC grade. CINSARC is especially informative in patients with intermediate-grade tumors, i.e. about 40% of all STS, for whom FNCLCC grade is poorly informative. In this population of uncertain prognosis, CINSARC identified around 50% of patients as having a high risk of metastatic relapse [10]. These patients have a more than 60% risk of metastatic relapse, as compared to 20% for LR-CINSARC patients. These rates are similar to what is reported in grade 3 tumors, confirming that CINSARC identifies HR patients regardless of FNCLCC grade.

Until recently, the main clinical hurdle for using CINSARC was technical, since it was performed on frozen tumors analyzed by microarrays, features incompatible with usual routine settings. It was first used with formalin-fixed, paraffin-embedded (FFPE) RNA sequencing [11], and is now fully evaluable in FFPE tumors using Nanostring technology [12]. Nanostring is a recent technology with two major advantages: only needs small quantities of tumoral DNA (feasible in microbiopsies), and perfect reproducibility between different machines and centers. Optimization of CINSARC in FFPE samples using NanoString (named NanoCind®, patent number EP18305190.3) is the final step for considering the use of CINSARC on diagnostic FFPE microbiopsies in routine settings for patients with localized STS, and it can now be used to guide treatment [13].

### Research hypothesis

Chemotherapy is currently not part of the treatment of patients with grade 1/2 (G1/2) localized STS, because they are not considered as being at high risk of relapse according to the classical factors. Since chemotherapy is considered beneficial in HR-STS patients, we hypothesize that CINSARC could be the key to identifying these patients differently and proving once and for all the benefit of chemotherapy in G1/2 STS. Our hypothesis is that in G1/2 STS patients considered as HR according to the CINSARC signature, the addition of four cycles of perioperative doxorubicin-based chemotherapy could improve metastasis-free survival (MFS) as compared with standard management.

## Methods and design

### Trial objectives

#### Primary objective

The primary objective of this study is to demonstrate whether adding four cycles of perioperative doxorubicin-based chemotherapy (combination of doxorubicin and ifosfamide/dacarbazine) improves MFS as compared with standard management in patients with resectable FNCLCC G1/2 STS, considered as HR according to CINSARC.

#### Secondary objectives

Secondary objectives include the comparison of the two therapeutic strategies in HR-CINSARC patients with G1/2 resectable STS in terms of disease-free survival (DFS), overall survival (OS) and safety profile. Moreover, the prognostic value of CINSARC in G1/2 STS treated by standard treatment is evaluated prospectively.

### Trial design

This is a phase III, multicenter, randomized open-label comparative study that has been designed to demonstrate whether adding four cycles of perioperative doxorubicin-based chemotherapy (doxorubicin and ifosfamide or dacarbazine) improves MFS as compared with standard management in patients with resectable FNCLCC G1/2 STS, considered as HR according to CINSARC (ClinicalTrials.gov Identifier: NCT04307277).

After providing written informed consent, patients considered as eligible for the CHIC-STS study by the investigator will be enrolled and molecular screening will be performed to determine their classification according to CINSARC (LR or HR). To evaluate both the effect of chemotherapy in the subgroup of patients with an HR-CINSARC signature and the prognostic value of the CINSARC signature, this study is based on a target selection design [14]. Patients for whom tumor material has been qualified and CINSARC classification has been determined will be definitively enrolled according to their CINSARC classification results (Fig. 1).
Patients classified as HR by CINSARC signature (HR-CINSARC) will be randomized between standard of care (surgical excision +/− external radiotherapy) and the experimental arm (standard of care with chemotherapy)Patients classified as LR by CINSARC signature (LR-CINSARC) will be treated at the discretion of the clinicians and data will be collected prospectively.

**Fig. 1 Fig1:**
[figure not shown]
Study design of CHIC trial

### Clinical study endpoints

#### Primary endpoint

The primary endpoint is MFS, which is defined as the delay between randomization and the onset of metastatic disease or death from any cause [15]. In the event of initial locoregional relapse, patients will be censored at the date of onset. Patients still alive at the time of analysis (including lost to follow-up) without onset of metastatic disease will be censored at the last disease assessment date.

#### Secondary endpoints

DFS is defined as the delay between randomization and first relapse (local, regional, or distant) or death from any cause. Patients still alive at the time of analysis (including lost to follow-up) without relapse will be censored at the last disease assessment date.

OS is defined as the delay between randomization and death from any cause. Patients still alive at the time of analysis (including lost to follow-up) will be censored at the last known date alive.

Safety will be assessed by the toxicity grading system of the National Cancer Institute (NCI-CTCAE v5.0).

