### Screening and randomization

The target population is patients with resectable FNCLCC G1/2 STS. After giving their written informed consent, patients fulfilling all inclusion and non-inclusion criteria (Table 1) will be enrolled in the study and molecular screening will be performed. After inclusion, an archived FFPE tumor sample of sufficient quantity will be sent to one of the four identified CINSARC signature platforms. Results of CINSARC analysis classifying patients as HR or LR-CINSARC will be provided by email to the investigator. After fulfilling additional inclusion criteria (HR-CINSARC signature, external radiotherapy not initiated before randomization (if applicable), full details in Table 1)), HR-CINSARC patients will be randomized by the sponsor to one of the two arms in a 1:1 ratio. Randomization will be stratified on the following factors: center, FNCLCC grade (grade 1 vs grade 2), tumor size (< 5 cm vs ≥5 cm), timing of chemotherapy envisaged (neo-adjuvant vs adjuvant) and histology (undifferentiated pleomorphic sarcoma vs dedifferentiated liposarcoma vs leiomyosarcoma vs synovial sarcoma vs other). A dynamic randomization procedure by minimization will be used. Randomization will be performed centrally by the IUCT-O clinical trials office using the TENALEA Clinical Trial Data Management System (online secure internet).

**Table 1 Tab1:** Inclusion and non-inclusion criteria

Inclusion Criteria	Non Inclusion criteria

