- The regional platform will transmit the CINSARC status to the sponsor and will be provided to the investigator.According to FNCLCC grading system, grade 2 and grade 1 tumors - Resectable and localized disease after appropriate extension work-up (including at least a chest-CT) - Available archived FFPE tumor sample in sufficient quantity to allow CINSARC qualification - Age ≥ 18 years - Eastern Cooperative Oncology Group (ECOG) performance status ≤2 - Life expectancy of at least 12 weeks after the start of the treatment - Women should be post-menopaused or willing to accept the use an effective contraceptive regimen during the treatment period and at least 12 months after the end of the treatment period. All non-menopaused women should have a negative pregnancy test within 72 h prior to registration. Men should accept to use an effective contraception during treatment period and at least 3 months (Ifosfamide treatment) or 6 months (Dacarbazine treatment) after the end of the study treatment - Signed written informed consent - Patient affiliated to a Social Health Insurance in France **Additional criteria: Randomized Part** - High-risk CINSARC signature -External radiotherapy not initiated before randomization (if applicable). -Acceptable hematologic function (within 72 h prior randomization): Absolute neutrophil count (ANC) ≥ 1.5 G/L, Platelet count ≥100 G/L and Hemoglobin > 9 g/dL -Acceptable renal function within 72 h prior randomization: Serum creatinine ≤1.5 x ULN or calculated creatinine clearance ≥60 mL/min (by the Cockcroft and Gault formula) -Acceptable liver function: Bilirubin ≤1.5 x upper limit of normal (ULN), AST (SGOT) and ALT (SGPT) ≤ 2.5 x ULN -Normal LVEF (> 50%) measured by echocardiography or isotopic ventriculography	- Soft-tissue sarcoma with the following histological subtypes: well-differentiated liposarcomas, alveolar soft-part sarcoma, dermatofibrosarcoma protuberans, clear-cell sarcoma, epithelioid sarcoma, alveolar or embryonal rhabdomyosarcoma - Primitive cutaneous, retroperitoneal, uterus or visceral STS - Metastatic disease - Previous or ongoing treatment for the sarcoma (with the exception of a surgery for diagnosis intend) - Contra-indication for Doxorubicin, Ifosfamide and Dacarbazine treatments - Prior therapy with ifosfamide or cyclophosphamide or other nitrogen mustards, and prior therapy with anthracyclines - Prior mediastinal/cardiac radiotherapy - History or presence of clinically relevant cardiovascular abnormalities such as uncontrolled hypertension, congestive heart failure NYHA classification of 3, unstable angina or poorly controlled arrhythmia, myocardial infarction within 6 months prior to study entry - Prior or concurrent malignant disease diagnosed or treated in the last 2 years except for adequately treated in situ carcinoma of the cervix, basal or squamous skin cell carcinoma, or in situ transitional bladder cell carcinoma - Active, uncontrolled bacterial, viral, or fungal infections, requiring systemic therapy - Known infection with HIV, hepatitis B, or hepatitis C - Women who are breastfeeding, pregnant or who plan to become pregnant while in the trial - Concomitant disease or condition that could interfere with the conduct of the study, or that would, in the opinion of the investigator, pose an unacceptable risk to the subject in this study - Patient who has forfeited his/her freedom by administrative or legal award or who is under legal protection (curatorship and guardianship, protection of justice) - Patient unable to comply with the protocol for any reason.

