### CINSARC analysis

For each patient, a representative sample formalin-fixed paraffin-embedded (FFPE) tumor block from sarcoma tumor surgical resection or biopsy specimen (archived tissue) will be selected for molecular screening. Quality control of samples will be assessed by the investigational site pathologist and samples with less than 50% of tumor cells will be considered as non-eligible for CINSARC analysis (screen failure). Tumor samples passing quality control will be addressed to one of the four regional platforms.

CINSARC analysis will be performed using Nanostring technology [16, 17]. Briefly, unique multiplexed probes are made with two sequence-specific probes complementary to a 100-base target region per target mRNA. The capture probe comprises a target-specific oligonucleotide coupled with a short sequence linked to biotin. The reporter probe consists of a second 50mer target-specific oligonucleotide linked to a unique chain of dye-labeled segments for detection by the system. Our nCounter code set, named NanoCind®, includes a panel of 75 probes, including 67 distinct test probes derived from 67 distinct genes and eight housekeeping genes for normalization purposes. Probe sets were designed and synthesized by NanoString. Additional information concerning probes can be found in the patent, which is filed under the number EP18305190.3. This raw data can be uploaded to a web interface developed for this study and hosted by the Institute Claudius Regaud. The interface will calculate the CINSARC status: “LR” or “HR”. The regional platform will transmit the CINSARC status to the sponsor, who will send it in turn to the investigator.

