#### Experimental treatment

Patients classified as HR-CINSARC randomized to the experimental treatment will be treated by standard of care with the addition of chemotherapy. They will receive 4 cycles of 3 weeks of intravenous chemotherapy with doxorubicin (20 mg/m2 per day [day 1, 2 and 3] every 3 week) in combination with dacarbazine (300 mg/m2 per day [day 1, 2 and 3] every 3 week)) for leiomyosarcoma or ifosfamide (3 g/m2 per day [day 1, 2 and 3] every 3 week) for other histologic subtypes.

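### DFS runs from randomisation but counts only relapse or death, so in the neo-adjuvant stratum local failure before or at surgery is not an event when it occurs

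*Protocol article*

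**What the plan says.** Under Secondary endpoints, "DFS is defined as the delay between randomization and first relapse (local, regional, or distant) or death from any cause". Living patients "without relapse will be censored at the last disease assessment date". The event list is complete as written: relapse at any site, or death.

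Under Screening and randomization, one stratification factor is "timing of chemotherapy envisaged (neo-adjuvant vs adjuvant"). Table 1 requires "Resectable and localized disease after appropriate extension work-up (including at least a chest-CT") and excludes "Previous or ongoing treatment for the sarcoma (with the exception of a surgery for diagnosis intend").

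Under Experimental treatment, the chemotherapy lasts "4 cycles of 3 weeks of intravenous chemotherapy with doxorubicin" plus a second drug. Under Standard of care, radiotherapy may come before or after the excision.

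Secondary objectives lists DFS among the comparisons of the two strategies in the randomised patients.

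**The concern.** Relapse presupposes that the disease has been cleared. A patient randomised before surgery has not reached that state. If the tumour then becomes unresectable, or the operation leaves gross disease, nothing has relapsed. The literal rule keeps the patient event-free although local treatment has failed.

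No other efficacy endpoint fills the gap. MFS counts metastasis or death and censors at an initial locoregional relapse; OS counts only death. DFS is the one listed efficacy endpoint meant to register local failure, and loss of resectability while surgery waits is a local failure that bears directly on a perioperative strategy.

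The trial is also open-label. If sites must decide for themselves whether pre-operative growth counts as a local relapse, they may decide differently by arm.

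**Working it through.** **Step 1: who carries tumour at time zero.** The neo-adjuvant stratum does, by definition. Table 1 points the same way, since entry requires resectable disease and only diagnostic surgery may come first. For the adjuvant stratum the article is less clear: CINSARC analysis accepts a "tumor block from sarcoma tumor surgical resection or biopsy specimen (archived tissue"), so some patients may already have been resected.

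**Step 2: what the DFS rule does with each outcome after randomisation.**

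| Outcome before or at surgery | DFS event when it occurs? |
|---|---|
| Distant spread | Yes |
| Death | Yes |
| Primary grows and curative surgery is no longer possible | Not in the list |
| No resection because of disease | Not in the list |
| R2 resection | Not in the list |

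For the last three rows the event comes only with later metastasis or death; otherwise the patient is censored at the last assessment.

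**Step 3: do the arms differ in exposure?** Four cycles of 3 weeks make 4 × 3 = 12 weeks. In the neo-adjuvant stratum this interval can precede surgery in the experimental arm only. Pre-operative radiotherapy is open to both arms, so control patients may also wait with the tumour in place.

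**Step 4: the plan's own figures.** No event number, effect or power is given for DFS, so there is nothing to reproduce. The 101 events belong to MFS. They do reproduce: hazard ratio = ln(0.75)/ln(0.60) = 0.563, and Freedman's formula at one-sided 2.5% and 80% power gives 101. They do not bear on this point.

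**Step 5: sensitivity illustration. Every input except the arm size is assumed.**
- Arm size: 250/2 = 125.
- Neo-adjuvant share f: 25% to 75%.
- Pre-surgical local failure rate p in the chemotherapy arm's neo-adjuvant patients: 2% to 10%.
- True DFS events by 3 years: 50 of 125 in each arm (40%, borrowing the article's 60% MFS), so the true hazard ratio is 1.
- Missed patients have no later event, which is a worst case.

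Missed events in the chemotherapy arm = 125 × f × p. The range is 125 × 0.25 × 0.02 = 0.6 to 125 × 0.75 × 0.10 = 9.4.

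Apparent hazard ratio = ln(1 − a)/ln(1 − b), where a and b are the counted event proportions in the chemotherapy and control arms. With f = 50% and p = 5%, 3.1 events are missed and a = (50 − 3.1)/125 = 0.375. If control misses none, b = 0.40 and the ratio is ln(0.625)/ln(0.60) = 0.92.

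| Missed events in control, relative to chemotherapy | Apparent hazard ratio over the whole range (true value 1) |
|---|---|
| None | 0.98 to 0.77 |
| One third as many | 0.99 to 0.84 |
| Equal | 1.00 |
| Roles reversed, chemotherapy misses one third as many as control | 1/0.99 to 1/0.84 = 1.01 to 1.19 |
| Roles reversed, chemotherapy misses none | 1/0.98 to 1/0.77 = 1.02 to 1.30 |

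The split between arms sets the direction. The neo-adjuvant share and the failure rate set the size. The article gives none of the three.

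**The case against.** **The failures are not lost.** A reader might infer that a pre-surgical failure is never an event. That goes too far. Distant spread and death before surgery count, and a patient left with unresected or gross disease has an event at later metastasis or death. Sites might also record local growth as local relapse, since the follow-up schedule includes examination of the primary site. This stands: the literal effect is mainly a delayed or inconsistently coded event. It does not remove the problem, because a late or variable event date still affects a time-to-event comparison.

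**The chemotherapy arm need not be favoured.** A reader might infer this from the added 12 weeks. The documents do not support it as a conclusion. Control patients also await surgery and may have pre-operative radiotherapy, and R2 resection can occur in either arm without any wait for chemotherapy. If chemotherapy prevents pre-operative growth, the missed failures fall more heavily on control and the rule hides benefit. This stands in full.

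**This is an article.** A condensed report commonly leaves event coding to the full protocol or the analysis plan. That would answer a complaint of missing detail. Here the endpoint is stated as a closed list that does not fit patients randomised before surgery. If the full protocol already counts these failures, only the article's wording needs correction.

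**DFS is secondary.** It has no event target or decision rule in the article, and the stopping and success rules concern the primary analysis. This also stands and limits the consequence.

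**Conclusion.** The point holds as a poorly fitting endpoint definition. Taken literally, DFS does not register local failure before or at surgery when it happens in patients randomised with their tumour in place. Because time to surgery can differ by arm, the DFS comparison can be distorted.

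The documents support no direction and no size. The hazard ratios in the working show sensitivity to assumed inputs, with missed patients never having a later event; they are not estimates. A specific shift in the DFS hazard ratio, or a statement that the definition favours chemotherapy, would go beyond the text. With few neo-adjuvant patients the effect is near zero. The primary MFS test does not use this definition and is unaffected.

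**What to change.** Redefine the endpoint as time from randomisation to the first of:
- locoregional progression that prevents curative surgery;
- no resection because of disease, or R2 resection;
- local, regional or distant relapse after surgery;
- death from any cause.

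Call it event-free survival, or keep the name DFS with this definition. Apply it identically in both arms and both timing strata, and state the date on which each component counts.

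The cost is one definition in the protocol and analysis plan, plus a check that the case report form records resection outcome and the reason for any non-resection. Comparison with DFS from adjuvant-only trials becomes slightly less direct. Treatment, sample size and the primary analysis do not change. The change should be made before DFS by arm has been examined.
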